### Recruitment procedure

A research nurse at the stroke unit will monitor admitted patients via patient records according to the inclusion and exclusion criteria and together with a stroke physician decide whether the patient is suitable or not. With a computer program the stroke physician will allocate the participant to one of the two groups and report group affiliation to the massage therapist. The massage therapist will give the patient oral and written information about the study and informed consent will be obtained.

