#### Power analysis and group distribution

In all, this study will include a total of 50 participants with 25 participants in each group. The power analysis is based on the primary outcome anxiety assessed with the State-Trait Anxiety Inventory (STAI) instrument (total score 20 – 80). Based on results from a previous study [1], the assumption is to find a difference in score corresponding to 8. Twelve subjects in each group will have an 80 % probability of achieving a statistically significant difference at a 5 % level. The subjects are allocated to the groups consecutively and by using minimization the groups are balanced with respect to severity in anxiety assessed with State-trait Anxiety Inventory (STAI) [39] and disability assessed with a Modified Rankin Scale (mRS).

Sub-sample I will consist of 30 participants (15 from the intervention group and 15 from the control group) who will be invited to participate in an fMRI study to evaluate brain activity during motor task performance. The inclusion criteria will be unilateral hemispheric stroke, intracerebral ischemic or hemorrhage lesion, first-ever stroke and cortical and/or subcortical lesions verified by radiology and/or clinical diagnosis, and fulfill the criteria for fMRI used at the Umeå Center for Functional Brain Imaging (UFBI), Umea University. An earlier study [40] found that the sample is adequate to produce stable and replicable results.

For feasibility purposes, a sub-sample (II) of 10 participants will be tested for dexterity in a movement laboratory before and after intervention.

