**Fig. 2 Fig2:**
[figure not shown]
Flow chart including interventions and assessments related to sensorimotor function and health-related quality of life

A summary of outcome assessments in relation to hypotheses and assessment methods can be found in Table 1.

For describing the study group, disability after stroke will be assessed by the Barthel index [42] and mRS [43]. In addition, age, gender, location of lesion, and acute treatment (thrombolysis/thrombectomy) will be recorded.

In this study we will attempt to assess components of body function such as anxiety, pain, and stress response. To test **hypothesis I** we will assess anxiety (primary endpoint) with the State-Trait Anxiety Inventory (STAI) [39]. Traits (A-Trait) are found to be stable over time and not sensitive to occasional stressors. These will be used at BL, W2, and FU. States (A-State) are found to be sensitive for occasional stressors assessing current emotional state [39] and will be used before and after treatment at BL, at W1 and W2. Pain will be assessed with a Visual Analogue Scale (VAS) [44]. To test **hypothesis II** (stress responses) we will record HRV as a continuous recording of a single-channel electrocardiogram (ECG) during TM at BL, W1 and W2. Salivary cortisol and blood pressure will be assessed in the morning, before and after TM and in the evening at BL, W1 and W2.

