### Data analysis

Data will be analyzed with repeated measurement methods to compare the intervention group and the control group. Statistical regression models that adjust for background characteristics and account for correlated measurements for the same individual will also be used (e.g., mixed effects model and generalized estimating equations). Data will be analyzed by inter-group analyses using the Statistical Package for Social Science (SPSS). Effect size will be estimated with Cohen’s d. The analysis will be performed on an intention-to-treat basis.

HRV will be analyzed by automatic detection of heartbeats, then the R-R interval data will be derived and transformed into an evenly sampled heart rate time series. From this time series HRV will be analysed in the frequency domain where the relative influence of different spectral components will be determined. From the signal, the mean heart rate, the total spectral power (PTOT), and the power of the low-frequency (PLF; 0.04-0.15 Hz) and high-frequency (PHF; 0.15-0.40 Hz) will be calculated. The recording and analysis software has been developed at Department of Biomedical Engineering (DBE), Vasterbottens county council (VLL) and will be analysed in collaboration with DBE, VLL.

The fMRI data will be analyzed in collaboration with experts at the UFBI. The effects of TM on sensorimotor functions and brain activity over time will be studied and compared within and between the intervention and control groups. The analysis will be similar to an earlier fMRI study [56].

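### As written, the arm is allocated and disclosed to the treating therapist before consent, and no stated STAI or mRS measurement precedes the minimisation that uses them

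*Protocol article*

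**What the plan says.** Recruitment procedure describes one sequence. A research nurse screens records and will "together with a stroke physician decide whether the patient is suitable or not". Then, using a computer program, "the stroke physician will allocate the participant to one of the two groups and report group affiliation to the massage therapist". The section ends: "The massage therapist will give the patient oral and written information about the study and informed consent will be obtained".

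Power analysis and group distribution says that allocation is consecutive and that minimisation balances the groups on STAI anxiety severity and on mRS. It does not say which STAI subscale is used.

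Assessments schedules the trait scale at BL, W2 and follow-up. The state scale "will be used before and after treatment at BL, at W1 and W2". mRS is listed at BL, W2 and follow-up. Only the sensorimotor tests are listed at pre-baseline. Effects expected immediately after a session are assessed by the massage therapist, and longer-term effects by a blinded assessor.

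Data analysis states: "The analysis will be performed on an intention-to-treat basis".

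**The concern.** Allocation concealment has to last until the patient is irrevocably in the trial. Here the arm is known to the person who explains the study, and that person will also give the treatment. Without any intent to mislead, the therapist may present the trial differently to a patient destined for massage than to one destined for the inactive device. Those who enter the two arms may then differ in anxiety, motivation or expectation, in a trial whose primary outcome is self-reported anxiety.

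The minimisation raises a linked question. It needs a STAI and an mRS value for each patient before the program runs, but the schedule shows neither before BL. If a STAI is taken earlier, it is an unscheduled research questionnaire, and on the stated order it would come before consent. If it is not, the minimisation lacks one of its inputs.

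**Working it through.** **1. Order of steps (Recruitment procedure)**

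| Step | Who | Arm known to the therapist? |
|---|---|---|
| Suitability decided | Nurse and stroke physician | No |
| Allocation by program | Stroke physician | No |
| Arm reported | Physician to therapist | Yes |
| Information given | Therapist | Yes |
| Consent obtained | Not named | Yes |

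No other section gives a different order or says that the arm is withheld until consent.

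**2. Timing of the minimisation inputs**

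| Input | Needed | First scheduled |
|---|---|---|
| STAI, trait | Before allocation, if this subscale is used | BL |
| STAI, state | Before allocation, if this subscale is used | BL, before and after the session |
| mRS | Before allocation | BL |

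The state score at BL belongs to a treatment session, so it follows allocation. Trait STAI and mRS at BL are not placed relative to allocation.

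**3. Whether other features of the design repair this**

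- Blinded assessment protects measurement, not entry.
- Intention-to-treat cannot bring in patients who never consented, since they supply no data.
- Minimisation balances those allocated. If some allocated patients then do not enter, that balance is not guaranteed among those who do.

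**4. Size, as an illustration only**

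The plan gives no refusal rate, so there is no planned figure to reproduce. Assume that anxiety is normally distributed, that exactly the most anxious fraction p of one arm declines, and that nobody in the other arm does. The mean of that arm falls by φ(z)/(1 − p) SD, where z is the (1 − p) normal quantile:

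- p = 0.10: 0.1755/0.90 = 0.195 SD
- p = 0.15: 0.2332/0.85 = 0.274 SD
- p = 0.20: 0.2800/0.80 = 0.350 SD

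The article states no SD. Its planning figures (12 per group, difference of 8, 80% power, 5% level taken as two-sided) imply, by the normal approximation, SD = 8 × √(12/2)/(1.960 + 0.842) ≈ 7.0. At that SD, 10% to 20% refusal shifts mean baseline by 0.195 × 7.0 ≈ 1.4 to 0.350 × 7.0 ≈ 2.4 points.

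**5. What reaches the primary outcome**

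The primary outcome is change in STAI. With equal SDs and a linear relation, a baseline shift Δ produced by selection on baseline alone moves the difference in change by (1 − ρ)Δ, where ρ is the correlation between baseline and later score. For ρ between 0 and 1 this lies between all of Δ and none of it; the article gives no ρ. A model with baseline STAI as a covariate would remove this part, but not imbalance in traits that were not measured.

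**The case against.** The best defence is that this is a condensed article. It never states outright that allocation precedes consent, and the consent clause is passive and names no consent-taker. The assessment schedule is organised by hypothesis, so a score absent from it could still be taken at screening. Exclusion criteria has the nurse collecting information from patients and staff, so there is patient contact early on. The mRS could come from clinical records. Figures 1 and 2, which may hold timing detail, are not shown.

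Much of this stands, and it rules out three stronger readings that a reader might infer:

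- *The minimisation cannot work.* The text shows only that no stated measurement precedes allocation. That needs reconciling but does not prove the procedure impossible.
- *All baseline STAI scores are taken by someone who knows the arm.* This is clear only for the state scale, which is session-linked. The trait scale follows a BL, W2 and follow-up pattern that suggests the blinded assessor, and the text does not say who collects it.
- *Patients decline because they know they would get an inactive device.* No section says that patients are told their arm before consenting. Ethical considerations mentions that sham patients might feel deceived, which suggests that they are not told. The route that remains is the therapist's presentation.

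The defence does not remove the main point. The section describes a procedure step by step, and nothing elsewhere supports another order. If practice already differs, the same rewording is still needed.

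**Conclusion.** The point holds in this form: as written, allocation and disclosure to the treating therapist come before information and consent, and the sections on minimisation and assessment timing do not fit together. The documents show an opening for selective entry; they do not show that it happened.

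Its size cannot be given from the documents. The 0.19 to 0.35 SD shift in mean baseline rests on perfectly sorted refusal of 10% to 20% in one arm and none in the other, and is an upper-end figure. A reader might set the corresponding points against the 8-point target as a share of the effect. That compares a baseline mean with a difference in change, and the planned models adjust for background characteristics (which ones is not listed), so the shift would not carry over one for one.

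A reader might also conclude that the intention-to-treat population is undefined. The article states the principle. The exact definition of the set is commonly left to the analysis plan, which is not shown, so its absence is no finding. The point still merits correction because selection after allocation cannot be reliably undone in the analysis.

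**What to change.** Rewrite Recruitment procedure in this order:

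1. Suitability is decided; information is given and consent obtained.
2. STAI, with the subscale for minimisation named, and mRS are recorded while the arm is unknown to everyone.
3. The minimisation program is run.
4. Only then is the therapist told the arm.

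Align Power analysis and group distribution and Assessments with this, so that the time point of each minimisation factor is stated. Keep the pre-session state score at BL, because the before-and-after comparison needs it. If the state scale drives the minimisation, one additional administration is needed before allocation. If the trait scale does, its BL administration can be moved to before allocation.

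The cost is at most one short extra questionnaire per patient and a change in the order of steps, with no additional patients. Once consent precedes allocation, who takes it no longer threatens concealment, so the therapist need not be replaced in that role.

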### Intervention

In addition to ordinary care at the stroke unit, the interventions will be given by massage therapists experienced in TM. TM is a gentle massage with strokes on hands, arms, feet and legs with a pressure of 2.5 N which is more gentle than Swedish massage but harder than strokes performed with a soft brush. The speed of the strokes is about 1–5 cm/sec [20]. Hand massage is described by Snyder and co-workers [41]. During the massage, the subjects will lie on a bed in the ward, or if discharged, in their home. During treatment, no conversations will be initiated by the massage therapist. To assess if the massage intervention is effective beyond effects of expectation a sham treatment will be given to the subjects in the control group. The sham-treatment is a non-active transcutaneous electrical nerve stimulation (non-TENS), given while participants lie in bed with electrodes attached to the skin of the affected arm. The device will be manipulated in a way so that no electrical impulses will reach the electrodes. During treatment, the masseur will remain in the room without initiating any conversation. The treatments for both groups will start one week after the onset of stroke and last for 30 min each time, five days a week for two weeks. The choice to use non-TENS as a sham treatment is based on the fact that TENS has some commonalities to massage; TENS is a form of sensory stimulation, although different to massage, and can be applied to the same limbs that are treated in the massage treatment.

In case of progressive stroke symptoms or discomfort from the massage treatment the stroke physician will be contacted and the appropriateness of continuing the study will be discussed. Reasons for withdrawals will be recorded.

Since neither clinical experience nor research evidence give reasons to believe that the interventions risk patients’ safety, a data monitoring committee is not considered to be needed.

### Assessments

Some of the effects are expected to occur immediately after a TM session and will be assessed before, during, and after the intervention session by the massage therapist (Fig. 1) on three occasions: baseline (BL), after one week (W1), and after two weeks (W2). Other effects are expected to occur over time and will be assessed on four occasions by a blinded assessor without knowledge of group affiliation. One occasion is a pre-baseline assessment in order to exclude the possibility that differences between baseline and follow up are merely a training effect. Long-term effects will thus be assessed at pre-baseline (pBL), baseline (BL), and follow-up 2 months after baseline (FU) (Fig. 2).

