### Aim, hypotheses and primary and secondary outcomes

This study will evaluate possible effects of TM after stroke on health in the ICF domains. Specific purposes are to investigate the impact on: Body function by means ofAnxietyPainStress reactions
 Activities by means ofSensorimotor functionDisability
 Participation by means ofHealth-related quality of life

Our hypotheses are that TM after stroke will;decrease anxiety and pain (hypothesis I)decrease physiological stress responses (hypothesis II)increase sensorimotor function, which will be reflected in improved gross and fine motor skills and touch discrimination (hypothesis III)increase ability to perform activities in daily life (hypothesis IV)increase activity in contralateral sensorimotor areas and decrease redundant brain activity in motor-related areas. This will lead to more focused activity in motor-related areas, thus improving behavioural movement in the patients (hypothesis V)increase health-related quality of life (HRQoL) (hypothesis VI)

The primary outcome is change in anxiety measured by STAI. The secondary outcomes include pain, physiological stress responses by change in heart rate variability and salivary cortisol, gross and fine motor skills, grip strength, touch discrimination, quality in motor performance, activities in daily life, brain activity, and HRQoL (Table 1).

**Table 1 Tab1:** Outcome assessments in relation to hypothesis and assessment methods

Outcome area	Hypothesis	Outcome	Assessment method
Body function	Hypothesis I	Anxiety (primary endpoint)	The State-Trait Anxiety Scale, (STAI)
		Pain, intensity	VAS
	Hypothesis II	Heart rate variability	ECG
		Salivary cortisol	
		Blood pressure	
Activities	Hypothesis III	Touch discrimination (sensory skills)	Shape Texture Identification Test (STI)
		Gross dexterity (motor skills)	Box and Blocks
		Fine motor dexterity (motor skills)	Nine Hole Peg
		Grip strength (motor skills)	Jamar® Hydraulic Hand Dynamometer
	(Subsample II)	Quality in motor performance	High-speed cameras in Movement laboratory
	Hypothesis IV	Disability after stroke	Modified Rankin Scale, Barthel index
	Hypothesis V (subsample 1)	Brain activity during finger-tapping/movement	GE 3 T scanner (General Electric, USA).
Participation	Hypothesis VI	Health-related quality of life	Nottingham Health Profile (NHP)

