## Methods

### Design

This project is a prospective randomized open-labelled control trial with blinded evaluation (PROBE-design) of TM after stroke. Minimization will be used to create groups for intervention and control. Using minimization offers a way to stratify groups and ensure balance with respect to significant variables also in smaller samples. Minimization is considered to have an advantage in small trials (cf. [35]) and is an acceptable alternative to random assignment according to the CONSORT statement (http://www.consort-statement.org) and SPIRIT checklist (http://www.spirit-statement.org/spirit-statement/).

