**Fig. 1 Fig1:**
[figure not shown]
Flow chart including intervention and assessments of anxiety, pain and physiological parameters during a day, which will be repeated at BL, W1 and W2

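### Blinded evaluation is claimed for the trial but not shown for its primary outcome: A-State is assessed by the unblinded massage therapist, and no assessor is named for A-Trait

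*Protocol article*

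**What the plan says.** - **Design label.** The Design section calls the trial a "prospective randomized open-labelled control trial with blinded evaluation (PROBE-design) of TM after stroke". The abstract says the same.
- **Primary outcome.** Under Aim, hypotheses and primary and secondary outcomes: "The primary outcome is change in anxiety measured by STAI". Neither a subscale nor a time point is named.
- **Who assesses what.** The Assessments section makes two sets. Effects expected straight after a session "will be assessed before, during, and after the intervention session by the massage therapist", at baseline (BL), one week (W1) and two weeks (W2). Effects expected over time go to an assessor who does not know the allocation.
- **Where anxiety falls.** The Fig. 1 legend covers "assessments of anxiety, pain and physiological parameters during a day, which will be repeated at BL, W1 and W2". Later in the Assessments section, A-State "will be used before and after treatment at BL, at W1 and W2". Of the trait scale it says: "These will be used at BL, W2, and FU". The Fig. 2 legend, for the over-time set, names sensorimotor function and health-related quality of life, not anxiety.
- **What the therapist knows.** Under Recruitment procedure, the stroke physician tells the massage therapist the patient's group. Under Intervention, massage therapists give the treatment, and the masseur stays in the room during the sham.

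**The concern.** In an open-label trial, the PROBE label tells the reader that whoever ascertains the outcome does not know the arm. Here the label is attached to the whole trial, yet the outcome that decides it is not among those given to the blinded assessor. Anxiety and pain are subjective ratings. On session days they are taken by the person who has just delivered the massage or the sham and who knows which of the two is under test. Prompting, tone, or a patient's wish to please can then differ between arms, most plausibly in favour of touch massage. A positive result on state anxiety could not be cleanly separated from that effect. The article describes the trial as groundwork for a multicentre study, so the distinction matters for what follows.

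**Working it through.** **Step 1: cross-reading.** The finding rests on setting the statements side by side.

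| Item | State anxiety (A-State) | Trait anxiety (A-Trait) | Pain (VAS) |
|---|---|---|---|
| Occasions | Before and after treatment at BL, W1, W2 | BL, W2, FU | BL, W1, W2 (Fig. 1 legend) |
| In the therapist's session-day set? | Yes: same occasions, and anxiety is in the Fig. 1 legend | Not stated; FU lies outside the therapist's three occasions | Yes (Fig. 1 legend) |
| Assigned to the blinded assessor? | No | No | No |

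The therapist knows the allocation (Recruitment procedure) and delivers treatment (Intervention). If the primary outcome is A-State, its assessor is unblinded. If it is A-Trait, its assessor is unspecified. Blinded assessment is documented in neither case.

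The end of the Assessments section has the blinded assessor put ID codes on the paper forms. That happens after the answer is given, so it does not make the assessment blind.

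**Step 2: an SD for illustration.** The article gives no SD, so its 12 per group cannot be reproduced from stated inputs; only the SD it implies can be recovered. Inputs from Power analysis and group distribution: difference 8, 12 per group, power 80%, level 5% (taken as two-sided). Solving the two-sample t-test gives a standardised difference of 1.197, so SD = 8 / 1.197 = 6.68, about 6.7. The normal approximation gives 8 / [(1.960 + 0.842) × √(2/12)] = 7.0. SD 10 is added as an assumed wider value.

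**Step 3: false-positive rate under a differential bias b.** Take 25 per arm, no true effect, and a two-sided 5% t-test with 48 degrees of freedom (critical value 2.011). The standard error is SD × √(2/25): 6.68 × 0.2828 = 1.89, or 10 × 0.2828 = 2.83. The test statistic is non-central t with non-centrality b / SE, and the rejection probability is P(|T| > 2.011).

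| Bias b (STAI points, assumed) | b/SE at SD 6.7 | False positives | b/SE at SD 10 | False positives |
|---|---|---|---|---|
| 0 | 0 | 5% | 0 | 5% |
| 1 | 0.53 | 8% | 0.35 | 6% |
| 2 | 1.06 | 18% | 0.71 | 11% |
| 3 | 1.59 | 34% | 1.06 | 18% |
| 4 | 2.12 | 55% | 1.41 | 28% |

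The bias sizes have no source in the article. The planned analysis is a repeated-measures or mixed model, so this single t-test shows scale only.

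**The case against.** Five points can be made on the other side.

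1. **The endpoint is not fixed as A-State.** A reader might infer that the whole primary outcome is collected by the therapist around each session. The text does not support that: no subscale is named, the trait scale has no stated assessor, and its follow-up measurement is outside the therapist's occasions. This stands and limits the point. It does not rescue the label, because trait anxiety is not assigned to the blinded assessor either.
2. **The patient is the rater.** If STAI and VAS are self-completed, a patient who knows whether massage was given is the source of the rating, and a blinded collector cannot change that. This stands. It limits what the fix achieves, and is a further reason not to claim blinded evaluation for these scales.
3. **The sham balances much of this.** Both arms have the same session length and schedule, with the masseur present and not initiating conversation, and control patients may believe the device is active. It would therefore be too strong to infer that the sham leaves all courtesy bias in place; only the part that differs between arms distorts the comparison. But the sham does not blind the therapist, so a differential part remains possible.
4. **The percentages are hypothetical.** Correct. At 1 point the inflation is small (8% or 6%). They also do not separate therapist effects from the patient's own expectation, so they cannot show how much the fix would gain.
5. **The article is open about who assesses what, and says double-blinding is difficult with massage.** True, but that openness is what shows the label to be wider than the design delivers.

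**Conclusion.** The point holds in a limited form. The article claims blinded evaluation without restriction. Its own text gives the A-State part of the primary outcome, and pain, to a therapist who knows the allocation and delivers the treatment, and names no assessor for A-Trait. The primary outcome is therefore not shown to be assessed blind on either reading.

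The inconsistency is textual and needs no numerical assumption. The size of the resulting bias cannot be derived from the article. The range of about 6% to 55% false positives rests on assumed differential biases of 1 to 4 points, an SD back-solved from the power statement (6.7) or assumed (10), and a simple t-test. It should not be read as an estimate of this trial's error rate.

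**What to change.** 1. **A-State and VAS.** Keep the planned before/after-session timing. Have the patient complete the forms with the therapist absent and seal them, to be opened only by the blinded assessor, who already codes the forms. Moving A-State to single visits at BL and W2 would change the planned before/after quantity and is not needed.
2. **A-Trait.** State that the blinded assessor administers it at BL, W2 and FU. The summary of that assessor's occasions mentions four but lists only pre-baseline, BL and FU, whereas the test schedule later in the section includes W2; add W2 to the summary.
3. **Primary outcome.** Name the STAI subscale and time point, so that it is clear which procedure protects it.
4. **Label.** In the abstract and the Design section, claim blinded evaluation only for what the blinded assessor rates: the sensorimotor tests and health-related quality of life, as in the Fig. 2 legend, and disability only if it is expressly assigned to that assessor, which the text does not now do. Say that STAI and VAS are self-reports by patients who know which treatment they received.

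The cost is envelopes, a short written procedure and minor logistics, including for patients treated at home after discharge. The change removes therapist-related ascertainment bias. It does not remove the patient's own expectation, which should be stated as a limitation.
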